## Abstract

**Background:**

Inadequate and inappropriate complementary feeding are major factors contributing to excess morbidity and mortality in young children in low resource settings. Animal source foods in particular are cited as essential to achieve micronutrient requirements. The efficacy of the recommendation for regular meat consumption, however, has not been systematically evaluated.

**Methods/Design:**

A cluster randomized efficacy trial was designed to test the hypothesis that 12 months of daily intake of beef added as a complementary food would result in greater linear growth velocity than a micronutrient fortified equi-caloric rice-soy cereal supplement. The study is being conducted in 4 sites of the Global Network for Women's and Children's Health Research located in Guatemala, Pakistan, Democratic Republic of the Congo (DRC) and Zambia in communities with toddler stunting rates of at least 20%. Five clusters per country were randomized to each of the food arms, with 30 infants in each cluster. The daily meat or cereal supplement was delivered to the home by community coordinators, starting when the infants were 6 months of age and continuing through 18 months. All participating mothers received nutrition education messages to enhance complementary feeding practices delivered by study coordinators and through posters at the local health center. Outcome measures, obtained at 6, 9, 12, and 18 months by a separate assessment team, included anthropometry; dietary variety and diversity scores; biomarkers of iron, zinc and Vitamin B_12 _status (18 months); neurocognitive development (12 and 18 months); and incidence of infectious morbidity throughout the trial. The trial was supervised by a trial steering committee, and an independent data monitoring committee provided oversight for the safety and conduct of the trial.

**Discussion:**

Findings from this trial will test the efficacy of daily intake of meat commencing at age 6 months and, if beneficial, will provide a strong rationale for global efforts to enhance local supplies of meat as a complementary food for young children.

**Trial registration:**

NCT01084109

## **Background**

### Research Justification

Among preventive measures that would reduce the excess mortality for children under the age of five years, exclusive breast feeding and good quality complementary feeding have been listed as first and third, respectively, with a calculated 600,000 deaths per year preventable by good complementary feeding (i.e. 6% of deaths) [1].

Infants and young children bear the brunt of chronic malnutrition and suffer the greatest consequences, that is, the highest risks of morbidity and mortality [2-4]. The incidence of malnutrition rises sharply between 6-18 months of age and the deficits acquired are difficult to compensate for later in the survivors [5]. In 2003, WHO/UNICEF published a Global Strategy for Infant and Young Child Feeding [6]. This document re-emphasizes that lack of exclusive breastfeeding in the first half of infancy is a major risk factor for infant/childhood morbidity and mortality, which is then compounded by inappropriate complementary feeding. It further indicates that inadequate knowledge about appropriate foods and feeding practices is often a greater determinant of malnutrition than actual lack of food. Emphasis is also given to the provision of sound and culture-specific nutrition counseling to mothers of young children in the widest possible use of indigenous foodstuffs that will help to ensure the optimal safe use of local affordable foods [7]. Recent significant, though still incomplete, progress with breastfeeding practices has not yet been matched in the area of complementary feeding.

Most intervention studies have not addressed local food-based strategies for the prevention of micronutrient deficiencies, although there have been successful education interventions focused on increased diversity that have shown promising results [8-10]. Yet millions of young children, especially those among the rural poor, do not have access to fortified foods or supplements and are unlikely to do so in the foreseeable future, especially on a sustainable basis. The WHO has published guidelines for complementary feeding which recommend daily intake of animal source foods after six months of age, noting that vegetarian diets cannot meet nutrient needs unless nutrient supplements or fortified products are used [11]. Even with diversity, expert reviews have concluded that it is not possible to achieve adequate intakes of the 'problem nutrients', specifically iron and zinc, with plant-based diets alone [12].

The importance of including animal source foods (ASF) in complementary feeding has been emphasized by several investigators [13-17]; by international organizations including WHO [18-20]; by national ministries of health as in Guatemala [21]; and by national committees including those in the U.S. [22-24]. Although these recommendations are inconsistent in details and lack specificity in regards to age of commencement, type of ASF, and quantities, they are in agreement on the value of the inclusion of ASF. Meat consumption has been positively associated with psychomotor outcome in children up to 24 months of age [25]; with iron status in late infancy [26]; and with improved growth and cognitive function in school-aged children [27,28]. As recently emphasized by The World Bank [29], however, it is at a younger age, i.e. the first one to two years when most damage results from malnutrition and when prevention is likely to be the most beneficial. The transition from exclusive breast feeding to a diversified diet, which is essential to satisfy nutritional needs, is a particularly vulnerable time [6,18].

Before addressing the challenges of an effectiveness study, which will depend on the identification of local sources of affordable meat and successful behavioral change communication, an efficacy trial to evaluate the theoretical benefits of meat as a first and regular complementary food from age six months is being undertaken in four diverse settings with high baseline stunting rates.

### Background information on the trial

The complementary feeding (CF) trial is being conducted as a common protocol through the Global Network (GN) for Women's and Children's Health Research. Centralized training was provided to country coordinators, who then provided local training to field staff. All sites followed a written manual of operations; identical equipment and supplies were provided to and utilized by all sites; common data forms were used and all data were transmitted to the data coordinating center (DCC) for compilation and storage.

### Trial sites

The trial is being implemented in Guatemala (Institute for Nutrition of Central America and Panama, Guatemala City), Pakistan (The Aga Khan University, Karachi), Democratic Republic of Congo (DRC, Kinshasa School of Public Health), and Zambia (University Teaching Hospital/University of Zambia School of Medicine, Lusaka). Community clusters were identified in rural areas in Zambia and DRC, small rural towns in the Western Highlands of Guatemala, and in urban/peri-urban communities in Pakistan. Stunting rates of at least 20% were defined *a priori *as the primary inclusion criterion for cluster selection. A second criterion for inclusion was the general lack of exposure of the community to micronutrient-fortified products (e.g. cereal grain products, infant formulas) at the time of recruitment.

### Pilot research

Prior to initiating the trial, a pilot study was conducted to obtain information about typical infant and toddler feeding practices in the potentially participating communities. Specifically, breastfeeding practices and use of meats and other animal source foods, micronutrient-fortified products, and vitamin-mineral supplements were documented for 5-9 month old infants and 12-24 month old toddlers. Anthropometric measurements were also obtained on the toddlers, with the aim of documenting stunting rates ([name], [name], [name], [name], [name], [name], [name], [name], [name], [name] *et al*: Intake of meat is associated with less stunting in toddlers in four diverse low income settings, submitted).

## Aim, objectives, and hypotheses

The overall objective of this study is to improve the quality of complementary feeding, and thereby improve growth and development of young children in low resource settings. The specific aim of this project is to determine the impact of a daily intake of meat between 6-18 months of age on linear growth velocity, dietary diversity, brain growth and neurocognitive development, infectious disease morbidity, and micronutrient status in populations traditionally dependent on non-micronutrient fortified plant-based foods for complementary feeding. The comparison group is infants from similar communities who receive an equi-caloric micronutrient fortified rice-soy food supplement.

The *primary hypothesis *is that daily feeding of meat from 6-18 months of age will result in significantly greater linear growth velocity compared to that achieved by daily feeding of an equi-caloric micronutrient fortified cereal supplement with both arms receiving education messages to optimize complementary feeding practices. *Secondary hypotheses *to be tested are that infants consuming meat daily will 1) have higher dietary diversity and variety scores; 2) higher scores on developmental testing; 3) lower rates of infectious disease morbidity; and 4) higher indices of micronutrient status for iron, zinc, and Vitamin B_12_.

## Methods/design

### Design

The design is a non-masked cluster randomized controlled efficacy trial of a daily intake of lyophilized beef vs. an equi-caloric daily micronutrient fortified rice-soy based cereal from 6-18 months of age (Figure 1). Mothers and care providers of infants in both groups also receive three education messages during home visits by research workers and through illustrative posters for the home and posted at local health centers to reinforce selected features of WHO recommendations for complementary feeding [11]. An additional message to encourage exclusive breastfeeding until six months and to initiate complementary feeding at six months is given at the time of recruitment when the infants were three to four months of age.

**Figure 1 F1:**
[figure not shown]
**Consort Diagram**.

The intervention is delivered by Community Coordinators, who are research workers with training as auxiliary nurses or equivalent primary community health training. The Community Coordinators are responsible for distribution of the complementary foods to the participating mother and infant pairs in their corresponding community/cluster; teaching the mothers how to prepare the food; communicating the educational messages during home visits; collection of baseline data; monitoring participant compliance with intervention food; and collecting weekly infectious disease morbidity data.

Trained staff different from the intervention teams conduct standardized assessments of infants at 6, 9, 12, and 18 months of age. Assessments include anthropometric measurements; Infant and Child Feeding Index (ICFI) and its components: Food Variety Score (FVS) and Dietary Diversity Score (DDS) [30,31]; measures of neurocognitive development at 12 and 18 months; and biochemical indices of micronutrient status at 18 months.

### Cluster Randomization and Sampling

The DCC randomized participating clusters within each country to either the lyophilized meat or cereal intervention using toddler stunting rates as the matching criterion; all clusters had stunting rates greater than 20% (Figure 1). Records of all births within each cluster were obtained from the Global Network Birth Registry or through local health center records by senior team members starting as soon as cluster randomization was completed and continuing as long as necessary to enroll the goal number of infants. Each month, a list of potential participants was randomly selected from these records for screening and recruitment.

### Intervention

#### Test group: Meat Supplement

A cooked, diced, lyophilized beef product is provided for daily consumption. It was expected that the infant would consume the initial target quantity of 15 g lyophilized beef/day by 7 months of age. Fifteen grams of the lyophilized beef is equivalent to 30 grams of cooked meat. The daily portion of lyophilized meat is increased to 22.5 g per day at 12 months of age. The lyophilized product is easily crumbled into a powder, which, when moistened, provides a paste or puree consistency that is readily consumed by a young infant. For older infants and toddlers, the cubes are mixed in with other foods or eaten dry as a "finger food." Mothers and care providers are taught age appropriate preparations of the product by the community coordinators during home visits. In the early weeks of the study, the meat was offered to the infant as the only complementary food or with a minimum of other foods, in order to achieve the intake goal of 15 g per day. The nutrient content of the lyophilized beef is provided in the Table 1.

**Table 1 T1:** Nutrient composition per daily serving of rice-soy cereal and lyophilized beef

Nutrient	6 - 12 mos of age			13 - 18 mos of age		
	**Cereal***	**Beef**	**RNI per day**	**Cereal***	**Beef**	**RNI per day**

Serving Size, g, uncooked	20	15	NA	30	22.5	NA

*Macronutrient Composition*						

Energy, Kcal	70	70	NA	105	105	NA
Protein, g	3.07	13	NA	4.60	19.5	NA
Fat, g	0.13	1.7	NA	0.19	2.5	NA
Carbohydrate, g	13.92	0	NA	20.89	0	NA

*Minerals*						

Zinc, mg	2.2	2.0	2.5 - 4.1	3.3	3	2.4 - 4.1
Iron, mg	5.5	1.4	6.2	8.3	2.1	3.9
Copper, mg	0.12	0.02		0.18	0.03	
Selenium, μg	4	NA	10	6	NA	17
Magnesium, mg	20	4.5	54	20	0.7	60

*Vitamins*						

Riboflavin, mg	0.07	0.06	0.4	0.11	0.09	0.5
Thiamine, mg	0.07	0.02	0.3	0.11	0.03	0.5
Niacin, NE	1.2	0.6	4	1.8	0.9	6
Vitamin B6, mg	0.09	0.06	0.3	0.5	0.09	0.5
B12, μg	0.10	0.56	0.5	0.15	0.84	0.9
Vitamin C, mg	70	0	30	105	0	30
Pantothenate, mg	0.14	0.08	1.8	0.21	0.12	2.0
Biotin, μg	0.58	N/A	6	0.87	NA	8
Folate, DFE, μg	17	1.3	80	26	2.0	160
Vitamin E (α-TE), mg	2	NA	No RNIs	3	NA	No RNIs

*Source: All micronutrient fortification levels in cereal are based on recommendations by Lutter and Dewey [32] for 6-23 mo olds.

The lyophilized meat used at all sites in this study is commercially prepared and marketed by Mountain House, Inc (Portland, Oregon, USA). The contents are stable for 15-20 years if the can is unopened and stored in temperatures less than 100°F. Once opened, the product is useable for up to 10 days when stored at room temperature. The manufacturer obtains meat only from US sources. A United States Department of Agriculture (USDA) inspector is on premises at the plant at all times to certify the quality and safety of the product, resulting in an USDA seal of certification on all cans. An international halal certification was obtained from the Islamic Services of America for the meat exported to Pakistan for use in the study. This certification signifies the compliance with the most stringent guidelines for the animal sacrifice, and cooking and packaging of the meat product.

The lyophilized beef was shipped from the U.S. "door to door" in a single lot to each participating site. Sites identified a secure, temperate (< 100°F) facility in which to store the cans of meat. Each site was responsible for obtaining import permits specific for their country.

From the 476 gram cans of lyophilized meat one member of the research staff weighs out daily portions of lyophilized meat into small zip-lock plastic bags (appropriately labeled and provided by study).

#### Comparison Group: Micronutrient Fortified Rice-Soy Cereal Supplement

The cereal supplement portion is iso-caloric to the meat supplement and provides approximately 70 kcal/day in a 20 g (uncooked) portion size, which is increased to 30 g/day when the infant reaches 12 months of age to match the energy provided by the increased portion of meat. The product, which was formulated specifically for this study by Nutrica, Inc (Guatemala City, Guatemala), is a mixture of pre-cooked rice and soy flour, fortified by the manufacturer according to recent guidelines for multiple micronutrients in complementary foods for 6-23 month olds [32]. Nutrient composition of 20 g and 30 g portions of the rice-soy mix are given in Table 1. The zinc and iron concentrations of the cereal mix were verified by laboratory analysis at the University of Colorado Denver.

According to the manufacturer preparation specifications, the 20 g serving, provided as a single-serving packet, is dissolved in ~120 ml clean water, brought to a boil and allowed to cook over low heat for 1-2 minutes prior to consumption. Pilot studies of preparation and acceptability in each site demonstrated good acceptance.

To increase sanitation and protection from pests, participants in both intervention arms are provided a tightly sealed container in which to store the weekly supply of food packets. A small metal cooking and serving pan (Sierra Cup™, Coghlan's Ltd.,

Winnipeg, MB, Canada) and a plastic infant spoon are also provided for infants in both groups; these both fit in the container along with the study food. Pictorial instructions for food preparation (specific to the assigned study group) and hand-washing (mother and infant) are affixed to the sealable container.

The week's supply (7 portions) of the meat or cereal is delivered to homes by community coordinators or their assistants. Intervention food preparation and consumption by the infant are observed during home visits by the research staff on a daily basis for the first two weeks of the intervention; 3 times per week for the first 3 months; and then weekly for the remainder of the intervention. During these home observations, intake of study food is recorded. If the infant does not consume the entire daily allotment at the observed feed, the mother is asked to safely store any remaining meat and to offer it to the same child later in the day.

Compliance is monitored for both study foods by counting and recording the number of unused packets (zip-lock or cereal packages) at the time of delivery of the next week's supply.

### Dissemination of Three Selected Education Messages

Both treatment groups receive three educational messages to encourage proper infant and child feeding. The educational messages were adapted from the *Guiding Principles for Complementary Feeding *[11] and other WHO educational materials [18]. The three messages are to: 1) feed thickened gruels every day; 2) feed the infant/toddler complementary foods (in addition to breastfeeding) at least 3 times a day; and 3) choose a variety of local foods for the infant/toddler. For both arms and all communities, posters were developed specifically for this study. The words were translated into the local language, and pictures were tailored to the local culture. Small posters are provided to all participating families, and identical larger posters are placed in local health centers to reinforce the messages and principles. Community health workers introduce these concepts one at a time as progressively appropriate for the infant's developmental stage, and as the mothers mastered each skill.

### Staff Training

After an initial introduction to the goals and objectives of the study research teams at a Global Network Steering Committee meeting, representatives of each of the participating sites traveled to the University of Colorado Denver for comprehensive training. Training modules included research ethics; procedures for recruitment, informed consent and enrollment of mothers and infants; instructions for storage, dispensing, and preparation of study foods; administration of data forms, including the administration and scoring of the Infant Child Feeding Index; and training relating the three education messages to infant feeding development and the principles of responsive feeding. and monitoring compliance of study procedures. Training and certification in anthropometric measurements and use of the equipment provided by the study were conducted. Staff was also familiarized with the developmental tests, as described in more detail below. Procedures for venipuncture and handling blood samples, including precautions to avoid zinc contamination of samples, were also demonstrated and written instructions were provided.

The Global Network Senior Foreign Investigators and country coordinators were provided the materials required to replicate training of community coordinators and other staff at their sites. Training was specific for the intervention teams and for the assessment teams in order to focus on the necessarily different skills required for data collection. The lead Global Network team (Colorado-Guatemala) and RTI provided technical assistance throughout the training to ensure that training was properly conducted and procedures were standardized.

### Study Subjects and Enrollment

When infants were 3 months of age, caregivers were approached by community coordinators, in the order on the list of randomly selected potential participants generated by the DCC, to recruit for participation in this study. Thirty infants per cluster provided informed consent and were enrolled over a period of approximately 10 months.

Inclusion criteria for individual families were to have an infant aged 3-4 months who was exclusively or predominantly breastfed and with the mother's intent to continue breast feeding through at least one year. Exclusion criteria were any family receiving or likely to receive free or subsidized complementary foods (or infant formula) through the health system or non-governmental organizations, and those who were feeding or intended to feed fortified infant formula or micronutrient-fortified commercial complementary foods. Exclusion criteria for individual infants were congenital anomaly; infant of multiple births; or neurological deficit apparent at the time of enrollment.

This research study was reviewed for approval by the Institutional Review Board (IRB) of each participating institution. All participants gave informed consent prior to enrollment into the study.

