### Data analyses

All analyses will be conducted using the intent to treat approach. The primary analysis will be adjusted only for clustering (the community effect). This adjustment for clustering also adjusts for community or site differences. A comprehensive analysis of baseline variables of the two treatment groups will be performed to assess the extent, if any, of baseline imbalances between the two groups of clusters/communities assigned to the two treatment groups, both at the individual and at the cluster levels, to determine the need for adjusting analyses. The baseline variables to be examined include: gender and socioeconomic status (SES), prevalence of exclusive breast feeding at 6 months, birth weight, maternal stature, parity, and site. Imbalances occurring at the cluster level can also be adjusted for by incorporating cluster level covariates, which may be cluster aggregated versions of the co-variables mentioned above.

For analysis of the primary outcome, the WHO Multicentre Growth Reference Study [38] will be used as a comparison. Mean Z-scores at 6, 9, 12 and 18 months for length-for-age, weight-for-age and weight-for-length will be determined as well as changes in Z-scores over 12 months. Linear growth velocity from 6-18 months of age was selected as the primary outcome measure because of its potential to be statistically more powerful than a cross-sectional comparison of length at 18 months alone.

The statistical analyses of the primary outcome and other comparison between treatment groups will use hierarchical or multi-level models to adjust for the cluster randomized design of the study. Hierarchical modeling provides a straightforward framework to accommodate adjustments for potential covariates and confounders, both at the subject level (e.g., birth weight, gestational age, gender, etc.) and at the cluster/community level (average SES at the community level, community access to prenatal and antenatal care, community exposure to other nutrition messages, etc.). For both 18-month and longitudinal outcomes, linear mixed models will be used for continuous outcomes such as growth parameters, whereas generalized linear mixed models will be used for discrete outcomes such as frequency of various nutritional intakes and incidence of morbidities.

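### Infants were recruited after open cluster allocation by the staff who deliver the food, so selection by arm is possible; the primary model should fix its covariates in advance rather than adjust only for clustering

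*Protocol article*

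**What the plan says.** All references are to the protocol article.

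- **Masking (Design).** "The design is a non-masked cluster randomized controlled efficacy trial".
- **Timing (Cluster Randomization and Sampling).** Birth records were collected "starting as soon as cluster randomization was completed and continuing as long as necessary to enroll the goal number of infants". From them, "Each month, a list of potential participants was randomly selected from these records for screening and recruitment".
- **Who recruits (Study Subjects and Enrollment).** When infants were 3 months old, "caregivers were approached by community coordinators, in the order on the list of randomly selected potential participants generated by the DCC".
- **Who delivers (Design, text after Figure 1).** "The Community Coordinators are responsible for distribution of the complementary foods to the participating mother and infant pairs". Each coordinator works in a particular cluster and also collects baseline data.
- **Eligibility (Study Subjects and Enrollment).** Some criteria are factual, such as age or multiple birth. Others depend on what a mother plans or what is expected to happen: "the mother's intent to continue breast feeding through at least one year", the likelihood of being given free or subsidised foods, and the intention to use formula or fortified products.
- **Analysis (Data analyses).** "The primary analysis will be adjusted only for clustering (the community effect". Baseline variables are then compared between arms to decide whether adjusted analyses are needed. The list is gender, SES, exclusive breastfeeding at 6 months, birth weight, maternal stature, parity and site.

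**The concern.** Cluster randomisation protects the comparison of infants only if entry to the trial does not depend on the arm. Here recruitment followed an open allocation and was done by people attached to one cluster and its food. Two steps after the approach could differ by arm: the eligibility decision, where it rests on intent or likelihood, and the caregiver's acceptance.

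Final numbers would not reveal this. Recruitment continued until each cluster had its 30 infants, so an exclusion or refusal is made good by a later family on the lists. Equal cluster sizes are therefore compatible with unequal acceptance.

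If enrolled families differed between arms in characteristics that predict growth, a primary contrast without covariates would carry that difference. Deciding on adjustment after seeing the imbalance also leaves the primary model open to choice once data are in hand.

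**Working it through.** **1. The plan's own sample size, to fix the inputs.** From Power Analyses: difference 0.3 SD, power 80%, two-sided 5%, ICC 0.05, cluster size 30, attrition 20%, and 2 clusters per arm for cluster loss.

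- Individually randomised: 2 × (1.960 + 0.842)² / 0.3² = 174.4, so 175 per arm.
- Design effect: 1 + (30 − 1) × 0.05 = 2.45, and 175 × 2.45 = 428.75.
- Attrition: 428.75 / 0.80 = 535.9, and 535.9 / 30 = 17.9, so 18 clusters.
- Cluster loss: 18 + 2 = 20 clusters and 20 × 30 = 600 infants per arm.

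This reproduces the stated size, which is not in dispute.

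**2. Precision of the primary contrast.** Take 20 clusters per arm and 24 infants analysed per cluster (30 × 0.80).

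- Design effect: 1 + (24 − 1) × 0.05 = 2.15.
- SE of the arm difference: √(2 × 2.15 / (20 × 24)) = √(4.30 / 480) = 0.0946 SD.

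**3. What an assumed selection shift b would do.** The documents give no figure for b, so the values below are assumptions. With no true effect, the two-sided rejection probability is 1 − Φ(1.96 − b/SE) + Φ(−1.96 − b/SE). If the shift runs against meat, power at a true 0.3 SD is Φ((0.3 − b)/SE − 1.96).

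| Assumed b (SD) | Share of 0.3 SD target | Error rate, normal | Error rate, t with 38 df | Power at 0.3 SD if b runs against meat |
|---|---|---|---|---|
| 0 | 0% | 5.0% | 5.0% | 88.7% |
| 0.02 | 7% | 5.5% | 5.5% | 84.1% |
| 0.05 | 17% | 8.3% | 8.1% | 75.2% |
| 0.10 | 33% | 18.4% | 17.8% | 56.1% |

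With 18 clusters per arm, should the two allowed for loss drop out, the SE is 0.0998 SD. The error rate (normal) is then 7.9% at b = 0.05 and 17.1% at b = 0.10.

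**4. What the clustering adjustment can do.** Data analyses says that adjusting for clustering also deals with community or site differences. A cluster effect allows for correlation within clusters and widens the standard error, here by the factor √2.15. Each cluster belongs wholly to one arm, so a selection difference that follows the arm sits in the arm contrast itself, and the cluster effect does not take it out.

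**The case against.** The strongest case on the other side has five parts.

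- **Key steps are inferred.** A reader might infer that coordinators ruled on eligibility knowing the arm and that families accepted or refused a named food. The article says only that coordinators approached families to recruit them. It does not say who decided eligibility or whether the arm was disclosed before consent. Coordinators' knowledge of the arm is a reasonable inference from the open design and the timing, but it is not stated. A manual of operations and central training in recruitment and consent are mentioned, and the manual is not shown. This stands, so the point is that selection was possible, not that it happened.
- **Features of the design limit the bias.** Clusters were chosen for low exposure to fortified products, so that criterion should exclude few families. Both arms receive a free equi-caloric food, the same utensils and the same messages. The outcome is velocity from 6 to 18 months, so selection on attained size does not carry over directly. Assessors are separate from the delivery staff. These features may shrink a bias but do not exclude one.
- **Adjustment is already foreseen.** A reader might infer that the plan has no remedy. That is wrong: the baseline comparison and conditional adjustment are planned, and the covariates are already named. What remains is that adjustment depends on observed imbalance and lies outside the stated primary analysis. A separate analysis plan, not shown, may settle this.
- **The illustration is not evidence.** Any assumed shift inflates the error rate, and nothing in the documents supports a size or a direction. This stands.
- **Counts may already be reported.** Figure 1 is the CONSORT diagram and is not shown, so screening and refusal numbers cannot be called absent.

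**Conclusion.** The concern holds in a limited form. Recruitment followed an open cluster allocation, the recruiters also deliver the food, and some criteria depend on intent or likelihood. Random list order does not protect the steps after the approach. The primary analysis as written would not correct a resulting shift in arm means, and it leaves covariate adjustment to depend on the data.

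The illustrated size, an error rate of about 8% to 18%, rests on an assumed shift of 0.05 to 0.10 SD, 20 clusters of 24 analysed infants per arm and ICC 0.05. The true size and direction are unknown.

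Two stronger conclusions are not supported. The documents do not show that the arms differ by selection. Nor do they support a change of recruiting staff as a useful remedy for this trial, because enrolment is described in the past tense. What is left is an inexpensive improvement to the analysis.

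**What to change.** In Data analyses, replace imbalance-triggered adjustment with a primary linear mixed model fixed in advance. It would contain the arm, the cluster effect, country/site, and the characteristics already listed there that predate recruitment: sex, birth weight, maternal stature, parity and SES. Exclusive breastfeeding at 6 months is also on that list but should stay out of this set, because it is observed after recruitment. State a rule for missing birth weight. Keep the clustering-only model as a sensitivity analysis.

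As supporting information, use the data coordinating center's ordered lists to tabulate by arm the numbers approached, ineligible by reason, and refused. This is the most direct evidence on whether entry differed.

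The cost is a little more analysis work, one table and the handling of missing birth weight. The covariates are ones that the plan already intends to examine. The limit is that adjustment addresses measured differences only, so selection through unmeasured attitudes or feeding intentions would remain.
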